### Data monitoring body

An independent researcher, who will be blind to the group allocations, will monitor any adverse effects and perform database management and statistical analyses. The treating therapists will be responsible for the monitoring of doses and compliance.

### Sample size estimation

Twenty-four participants will be recruited, with walking speed as the primary outcome. The sample size has been calculated, to reliably detect a between-group difference of 0.18 m/s in walking speed, with 80% power, at a two-tailed significance level of 0.05. In previous trials [9, 16, 25] with similar samples of community-dwelling people with Parkinson’s disease who received tDCS associated with walking training, the mean walking speed of the participants was 0.73 m/s (SD 0.15 m/s), measured by a timed-walking measure. The least number of participants needed to detect a 0.18 m/s difference between two independent groups, which would indicate a change in the UPDRS walking category [26], is 11 per group, i.e., 22 participants in total. Based on the assumption that about 10% of participants may drop out during the study, a target of 24 participants in total has been set.

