## Discussion

This trial will examine the efficacy of the addition of tDCS to walking training for improving walking, mobility, and falls in people with Parkinson’s disease. Although previous studies [9, 10, 15, 16, 27] have investigated the combined effect of tDCS and walking training, methodological shortcomings (e.g., design and very small sample sizes), characteristics of interventions (e.g., duration of intervention, type of exercises), and characteristics of the participants (e.g., level of disabilities) prevent drawing clear conclusions, which could help clinicians in their decision-making process. In addition, many trials did not investigate whether benefits carry over to improving mobility and falls. In response to this challenge, a triple-blinded randomized trial will be conducted. High internal validity is expected, due to randomization, concealed allocation, blinding of assessors, participants and therapists, intention-to-treat analysis [28], and appropriate sample size.

Previous studies suggest that tDCS modulates cortical excitability during stimulation by non-synaptic changes of the cells, and increasing evidence indicates that the aftereffects of tDCS are driven by synaptic modification [29]. Synaptic plasticity could, therefore, induce long-lasting excitability changes in the central nervous system. Although the neurophysiological effects of tDCS have been identified and its safety has been proved [29, 30], the clinical effects remain unclear. This trial focuses on identifying the effects of the addition of tDCS on walking parameters commonly affected in individuals with Parkinson’s disease [3, 31]. If neurophysiological benefits of tDCS are carried over to clinical benefits, clinicians will assure an important tool to help reduce disabilities related to the continuous death of dopamine-producing cells in the *substantia nigra*. Less expensive portable devices are currently available, making direct current potentially ideal as an adjunct to other physical interventions [30].

This trial has some limitations. The experimental and control interventions consist of walking exercises delivered three times per week over 4 weeks and, therefore, depend on participants’ motivation, adherence, and commitment. Strategies to encourage participants to comply with the protocol, such as contracts and phone calls, are planned.

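### For the two-group comparison described, the 80% power holds only under the normal approximation; with 21–22 completers it is about 74–76%

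*Protocol article*

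**What the plan says.** All inputs are in the protocol article, Methods, Sample size estimation. The aim is "to reliably detect a between-group difference of 0.18 m/s in walking speed", "with 80% power, at a two-tailed significance level of 0.05". The variability comes from earlier trials in which "the mean walking speed of the participants was 0.73 m/s (SD 0.15 m/s"). The calculation is framed as the number "needed to detect a 0.18 m/s difference between two independent groups", and the answer given "is 11 per group, i.e., 22 participants in total". After an allowance for about 10% dropout, "a target of 24 participants in total has been set". No formula, test or within-person correlation is named.

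The Randomization section sets 1:1 allocation. The Statistical analyses section plans a two-way (group by time) repeated-measures ANOVA, analysed by intention to treat. The Discussion faults earlier trials for being very small and lists among this trial's strengths "intention-to-treat analysis [28], and appropriate sample size".

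**The concern.** Two steps in the calculation look slightly optimistic, both in the same direction.

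- **Formula.** A standardised difference of 0.18/0.15 = 1.2 gives a very small trial. At that size the normal formula, which treats the SD as known, and a test that estimates the SD no longer agree. Eleven per group looks like the normal-formula answer.
- **Dropout.** Removing 10% of 24 leaves slightly fewer than the 22 that the section says are needed.

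The stake is how a null result is read. The article presents 0.18 m/s as reliably detectable and the sample size as a strength. If the comparison it describes has less than 80% power once the expected dropout has occurred, a non-significant result would be given somewhat more weight than it deserves.

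**Working it through.** **Inputs** (Sample size estimation): difference 0.18 m/s; SD 0.15 m/s; two-sided alpha 0.05; power 80%; two independent groups; dropout about 10%; target 24. Allocation 1:1 (Randomization). Standardised difference d = 0.18/0.15 = 1.2.

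**Step 1: reproduce the plan's figure.** Normal approximation:

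n per group = 2(z₀.₉₇₅ + z₀.₈₀)²/d² = 2(1.960 + 0.842)²/1.2² = 10.90, rounded up to 11.

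The same formula gives 80.4% power at 11 per group. The stated 11, 22 and 80% all reproduce.

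**Step 2: the same comparison with the variance estimated.** Two-sample t-test, noncentral t, with noncentrality d·√(n₁n₂/(n₁+n₂)) and n₁+n₂−2 degrees of freedom:

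| Analysed | Noncentrality | df | Critical t | Power |
|---|---|---|---|---|
| 11+11 | 1.2 × √5.5 = 2.814 | 20 | 2.086 | 76.3% |
| 10+11 | 1.2 × √(110/21) = 2.746 | 19 | 2.093 | 74.1% |
| 12+11 | 1.2 × √(132/23) = 2.875 | 21 | 2.080 | 78.3% |
| 12+12 | 1.2 × √6 = 2.939 | 22 | 2.074 | 80.2% |

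Solving for 80% power gives 11.94 per group, so 12. The difference detectable with 80% power is 0.188 m/s at 11+11 and 0.194 m/s at 10+11.

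**Step 3: dropout.** 24 × 0.9 = 21.6, against 22 required. In the other direction, 22/0.9 = 24.4, so 25 recruits, or 26 for equal arms. In whole people, losing 2 of 24 (8.3%) leaves exactly 22, and losing 3 (12.5%) leaves 21. About 10% dropout therefore means 21 or 22 completers. If they split as evenly as possible, power is 74.1% or 76.3%; two losses from the same arm (12+10) give 76.0%.

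**Step 4: both steps together.** To keep 80% for the unadjusted comparison after 10% dropout: 24/0.9 = 26.7, so 27 recruits, or 28 for equal arms, against 24 planned.

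**Step 5: what using the baseline could do.** The article gives no baseline-to-week-4 correlation r, so the values below are assumptions. All figures are for 10+11 completers.

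- Baseline-adjusted week-4 comparison, d/√(1−r²), one further degree of freedom lost (18): 77.7% at r = 0.3, 85.0% at 0.5, 95.3% at 0.7.
- Group-by-time contrast from baseline to week 4 (change scores), d/√(2(1−r)), 19 degrees of freedom: 60% at r = 0.3, 74% at 0.5, 83% at 0.6, 92% at 0.7.

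**The case against.** Several points on the other side are sound.

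**The 11 is not a miscalculation.** It follows from the stated inputs by a standard formula, and the article names no test that this would contradict. A reader might infer that the authors made an arithmetic error; Step 1 shows that they did not. What remains is that the approximation is about 4 points optimistic at this size. A least number is claimed, and any analysis that estimates the variance, as an ANOVA does, needs 12 per group for this comparison.

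**The dropout gap is under half a person on an approximate rate.** Two losses leave exactly 22. This stands: taken alone, the rounding is trivial. It matters only because it leaves no slack for Step 2.

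**Twelve per arm are recruited, and the analysis is by intention to treat.** If all 24 contribute data, power is 80.2%. This is true, and the article does not say how missing outcomes are handled. But the plan's own dropout step treats dropouts as lost to the calculation, and the loss of even one participant takes the figure to 78.3%.

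**The t-test is not the planned analysis.** This is the strongest point. A reader might infer that the trial will not have 80% power. The article does not support that: the planned repeated-measures ANOVA includes baseline and, as Step 5 shows, could exceed or miss 80% depending on a correlation that is not stated. The finding is therefore confined to the comparison that the sample size section describes, which uses a cross-sectional SD and no correlation.

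**Conclusion.** The concern holds in a limited form. For an unadjusted comparison of two independent groups with the article's own difference, SD and alpha, 80% power at 11 per group exists only under the normal approximation. With the variance estimated and the assumed dropout, power is about 74–76%, some 4 to 6 points lower, and the detectable difference is about 0.19 m/s. On that basis the target of 24 reaches 80% only with no dropout.

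This rests on three assumptions: SD exactly 0.15 m/s, analysis of completers only, and losses spread about evenly between the arms. It does not show that the planned ANOVA is underpowered, nor that the sample size is badly wrong. It shows that the power statement is not supported by the comparison it describes, and that any support the planned analysis might lend depends on a correlation left unstated.

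**What to change.** Keep 24 participants and correct the statement in one of two ways.

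1. **Restate the power.** Say that an unadjusted comparison with 21–22 completers has about 74–76% power for 0.18 m/s, and 80% only if all 24 are analysed.
2. **Change the basis of the calculation.** Use a baseline-adjusted comparison at week 4 and state the assumed baseline-to-week-4 correlation with its source. With 21 completers, power is then about 78% at a correlation of 0.3, 85% at 0.5 and 95% at 0.7. If this route is taken, the Statistical analyses section should name the same comparison as the primary one.

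In either case, qualify the Discussion's description of the sample size so that it matches the restated figure.

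The cost is wording. No extra participants are needed. Under the first option the stated power becomes slightly less favourable; under the second it rests on a correlation that must be justified.

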### Statistical analyses

Data collection will yield eight variables: walking speed (m/s), walking step length (m), walking cadence (steps/min), walking confidence (modified Gait Efficacy Scale score; 10–100), mobility (TUG; seconds), freezing of gait (New Freezing of Gait Questionnaire; 0–28), fear of falling (FES-I Brazil score; 16–64), and number of falls. There are two factors (group × time), with repeated measures on the time factor. Two-way analyses of variance with repeated measures at all time points for all outcomes will be reported to evaluate the statistical significance of the between-group differences. The mean between-group differences, along with 95% confidence intervals, will be reported for all outcomes. The effect of the intervention will be calculated based on intention-to-treat analyses.

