### Randomization

Randomization will be computer-generated, by a researcher not involved in participant recruitment, and stratified according to the baseline walking speeds: slow (≤ 0.5 m/s) and intermediate (0.51 to 1.0 m/s) walkers, to ensure an even spread between the groups (1:1 allocation). The allocation of the participants will be concealed in sequentially numbered and sealed in opaque envelopes, prepared prior to the study by a research assistant, who will not be involved in the study. After the baseline measures have been collected, participants will be randomly assigned to the experimental or control group by the treating therapist, after revealing the content of the sealed opaque envelopes. All outcomes will be measured by blinded assessors. All enrolled participants will receive a code, in order to protect confidentiality before, during, and after the trial.

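### Baseline walking speed enters the analysis as an outcome level and not as a covariate, which costs precision by an amount that depends on an unstated correlation

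*Protocol article*

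**What the plan says.** All places are in the protocol article.

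- **Design**: outcomes are taken at weeks 0, 4 and 8.
- **Randomization**: allocation is "stratified according to the baseline walking speeds", with slow walkers at or below 0.5 m/s and intermediate walkers from 0.51 to 1.0 m/s.
- **Statistical analyses**: the model has two factors, group and time, "with repeated measures on the time factor". It is a two-way repeated-measures analysis of variance covering all visits and all outcomes. Mean between-group differences with 95% confidence intervals are promised. No baseline covariate or stratum term is named, and the section does not say whether the between-group effect is the group main effect, the interaction or a contrast at one visit.
- **Sample size estimation**: the trial is sized to "detect a 0.18 m/s difference between two independent groups", with an SD of 0.15 m/s for walking speed itself, and the stated number "is 11 per group, i.e., 22 participants in total". Baseline plays no part in this calculation.

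**The concern.** Week 0 precedes treatment, so it carries no treatment effect. Its use is to explain variation between people at weeks 4 and 8. Making it a level of the outcome uses that information less efficiently than making it a covariate, and how much less depends on which contrast is read from the model. The sample size leaves little slack, so avoidable variance matters. The open choice of contrast adds to this, because one of the tests that the named model supplies averages the untreated visit into the effect.

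**Working it through.** **Inputs.** From Sample size estimation: effect 0.18 m/s, SD 0.15 m/s, two-sided 0.05, 80% power, 11 per group. From Randomization: 1:1 allocation. The correlation r between baseline and follow-up speed is not given, so I assume a range of 0.3 to 0.9. I also assume the same SD and a common r at all visits, and normal data.

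**1. The plan's own figure.** n per arm = 2 × (1.960 + 0.842)² × (0.15/0.18)² = 10.90, so 11. The stated number reproduces by the normal approximation. With the noncentral t distribution, power is 76% at 11 per arm and 80% at 12.

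**2. Variance of the week-4 effect**, relative to an unadjusted week-4 difference:

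- unadjusted week-4 difference: 1
- change from week 0 to week 4 (a group-by-time contrast): 2(1 − r)
- adjusted for baseline: 1 − r²

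The ratio of adjusted to change is (1 − r²) / [2(1 − r)] = (1 + r)/2. Adjustment therefore cuts the variance of the change contrast by (1 − r)/2, which is 35%, 25%, 15% and 5% at r = 0.3, 0.5, 0.7 and 0.9. It cuts the variance of the unadjusted difference by r², which is 9%, 25%, 49% and 81%.

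The SE of the unadjusted difference is 0.15 × √(2/11) = 0.064 m/s. At r = 0.5 the change contrast has the same SE, since 2(1 − 0.5) = 1, and the adjusted SE is 0.064 × √0.75 = 0.055 m/s.

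**3. Group main effect.** Averaging a sustained effect over three visits gives (0 + 0.18 + 0.18)/3 = 0.12 m/s. The variance of a person's mean is 0.15² × (1 + 2r)/3.

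**4. Power at 11 per arm** (noncentral t; 20 degrees of freedom, or 19 for the adjusted analysis, whose variance is also multiplied by 1 + 1/(22 − 4)):

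| r (assumed) | Unadjusted week 4 | Change, week 0 to 4 | Baseline-adjusted week 4 | Group main effect |
|---|---|---|---|---|
| 0.3 | 76% | 62% | 78% | 69% |
| 0.5 | 76% | 76% | 85% | 59% |
| 0.7 | 76% | 93% | 95% | 51% |
| 0.9 | 76% | >99% | >99% | 46% |

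Simulation with 40,000 trials per r agrees with the first three columns to within half a percentage point. At r = 0.9 the simulated SEs of the change and adjusted estimates are 0.0287 and 0.0288 m/s, so there is nothing to gain there over the change contrast.

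**5. The stratum.** With mean 0.73 and SD 0.15, the slow cut-off lies at (0.50 − 0.73)/0.15 = −1.53. Under normality about 6% fall at or below it, and 22 × 0.06 is about 1.4 people. Adding the stratum to the change analysis in simulation moved the 95% confidence half-width from 0.132 to 0.129 m/s at r = 0.5, and from 0.102 to 0.101 at r = 0.7.

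**The case against.** Repeated-measures analysis of variance is a conventional and valid method. Its group-by-time contrast works within persons, so a chance baseline gap is subtracted out, and randomisation keeps the contrast unbiased. If r is 0.7 or more, the change contrast already exceeds 90% power. So does the two-degree-of-freedom interaction test (66%, 81%, 96% and >99% at r = 0.3, 0.5, 0.7 and 0.9, under compound symmetry). The article is condensed, and covariates are often left to an analysis plan.

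Most of this stands. It limits the size of the point but does not remove it. The article does not leave the model open: it names a two-factor model with week 0 inside it. Nobody can rely on a high r in advance, and the 1.0 m/s entry limit may lower it.

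A reader might infer four stronger things that the document does not support:

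- **That adjustment lifts power from 76% to 95% or more.** The 76% belongs to an unadjusted week-4 difference. That is one possible reading of the promised mean differences, but the section does not name it as the test.
- **That adjustment always makes good the gap between 76% and the planned 80%.** At r = 0.3 it reaches 78%.
- **That adjustment is free.** It uses one or two degrees of freedom.
- **That leaving out the stratum seriously widens the standard errors.** On the protocol's mean and SD, few people are expected in the slow stratum, and the simulated change is small.

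**Conclusion.** The point holds as a loss of efficiency in a stated model. The treatment estimate is not biased. Against the change contrast the loss is material at r of about 0.5 or below, small at 0.7 and nil near 0.9. Against an unadjusted week-4 difference it grows with r. If the group main effect is taken as the test, power is 46% to 69% over the range tried, below the planned 80% throughout.

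The facts about the model are certain from the text. The size of the loss is not, because it rests on an assumed r, equal SDs, normal data and a contrast that the article does not identify. It does not follow that the trial will miss its planned power. Across the range tried, baseline adjustment is at least as good as either alternative estimate of the week-4 effect, apart from a negligible difference at r = 0.9, so it is the safer choice when r is unknown. The change should be made, but it is not a question of validity.

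**What to change.** Before unblinding, name the week-4 between-group difference in walking speed as the primary estimate. Estimate it and the week-8 difference with baseline speed as a continuous covariate, by analysis of covariance or a mixed model with baseline constrained equal between the arms. Adjust each other continuous outcome for its own baseline. State that the group main effect averaged over all three visits is not the treatment effect. A stratum term may be added, but for walking speed it is minor once continuous baseline speed is in the model.

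The cost is a change of wording and one or two degrees of freedom. No new data, visits or participants are needed.

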## Methods

### Design

A prospective, randomized controlled trial with concealed allocation, blinded assessors, participants and therapists, and intention-to-treat analysis will be carried out (Fig. 1). Community-dwelling people with Parkinson’s disease will be recruited from the general community, by means of advertisements and by screening public rehabilitation services and lists of previous observational or cross-sectional research projects. Participants will be randomly allocated into either experimental group (i.e., walking training with tDCS) or control group (i.e., walking training with sham-tDCS). Outcome measures will be collected by trained researchers at baseline (week 0), at the end of the intervention (week 4), and 1 month beyond the intervention (week 8). Measurements and interventions will be conducted during the on phase of medication. Analyses of the inclusion criteria, getting the informed consent, data collection, and statistical analyses will be carried out by researchers, who will be blind to the group allocation. All the participants will be evaluated and receive all the information regarding the interventions in a research laboratory. The study obtained ethical approval from the Institutional Research Ethical Committee (CAAE 06952819.6.0000.5060) of the Universidade Federal do Espírito Santo, Vitória, Brazil. The trial was prospectively registered at the Ensaiosclinicos.gov.br, Registry: RBR-6bvnx6 (www.ensaiosclinicos.gov.br/rg/RBR-6bvnx6/).

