The number of falls will be recorded by the use of a “falls diary” [24], and the proportion of fallers in each group will also be compared. All participants will receive weekly calendars on entry to the study, with instructions to record the following events: number of falls, visits by or to nursing and allied health personnel, and hospitalizations. Participants will be asked to return the completed calendar weekly to a researcher unaware of the group allocation.

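### Number of falls is assigned to a repeated-measures ANOVA over weeks 0, 4 and 8, but falls are recorded only from study entry, so the outcome has no week-0 level

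*Protocol article*

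**What the plan says.** All references are to the protocol article.

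- **Model.** Statistical analyses describes the structure as "There are two factors (group × time), with repeated measures on the time factor" and then says that "Two-way analyses of variance with repeated measures at all time points for all outcomes will be reported".
- **Scope.** The list of eight variables in the same section ends with "fear of falling (FES-I Brazil score; 16–64), and number of falls".
- **Effect measure.** "The mean between-group differences, along with 95% confidence intervals, will be reported for all outcomes".
- **Time points.** Design sets assessments at weeks 0, 4 and 8.
- **How falls are collected.** Secondary outcomes: "All participants will receive weekly calendars on entry to the study, with instructions to record the following events: number of falls". Completed calendars are returned weekly. No recalled or pre-entry count of falls is described.
- **Second falls measure.** The same section adds that "the proportion of fallers in each group will also be compared". This proportion is not among the eight variables.

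**The concern.** Walking speed, step length, cadence, the TUG and the questionnaire scores can all be measured at week 0, so a group-by-time layout with three levels fits them. Falls are different. They accrue over intervals, and recording starts when the participant enters. The article nevertheless fixes one model and one effect measure for every outcome and names falls among them. This is a stated choice that conflicts with the article's own description of data collection, not a detail left to another document.

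Falls appear in the research question (Background) and in the Discussion's account of what many trials did not investigate. If the stated analysis cannot be run on them, the analyst must decide during analysis which periods to compare, what to put in the week-0 cell and which test to use.

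**Working it through.** **1. The plan's own figures.** The article gives no fall rate, dispersion or power for falls, so there is no falls figure to reproduce. The sample size rests on walking speed alone: 2 × (1.96 + 0.84)² × 0.15² / 0.18² = 10.9, hence the stated 11 per group. It contains no falls input and is unaffected. The target of 24 at 1:1 allocation gives 12 per arm.

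**2. What can fill the three cells.**

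| Level | Walking speed | Number of falls |
|---|---|---|
| Week 0 | measured | nothing recorded yet |
| Week 4 | measured | diary, weeks 1-4 |
| Week 8 | measured | diary, weeks 5-8 |

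Two things can happen at week 0. If the cell is left empty, it is empty for all 24 participants and the three-level model cannot be fitted. If it is filled with zero, the following happens.

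**3. Effect of a structural zero.** Assume, for illustration only, 2 falls per 4 weeks in the control arm and a halved rate in the experimental arm. The cell means are then control (0, 2, 2) and experimental (0, 1, 1).

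- *Time effect.* The overall means are 0, 1.5 and 1.5. Falls appear to rise from baseline in both arms, only because counting had not begun.
- *Averaged group difference.* Over three levels it is (0 − 1 − 1)/3 = −0.67. Over the two real periods it is (−1 − 1)/2 = −1. The zero column shrinks it by one third.
- *Interaction.* The group differences by level are 0, −1, −1, so there is an interaction although the effect is the same in both real periods. Over the two periods they are −1, −1, and there is none.
- *Error degrees of freedom.* For the within-participant error, (24 − 2) × (3 − 1) = 44, against (24 − 2) × (2 − 1) = 22. The extra 22 come from a column of constants with zero variance.
- *Group F test.* Each participant's mean is multiplied by 2/3, so the between-group and between-participant sums of squares change by the same factor and F is unchanged.

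**4. Error rates by simulation.** Inputs, all assumed: 12 per arm, gamma-Poisson counts, mean 0.5 to 4 falls per 4 weeks, gamma shape 0.3 to 1.0, 3,000 runs per setting. Between 20% and 74% of period counts were zero.

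| Layout | Type I, group | Type I, interaction | Power for halved rate, group | Power for halved rate, interaction |
|---|---|---|---|---|
| Zero at week 0 plus two periods | 3.2-4.6% | 3.3-5.7% | 6-26% | 5-28% |
| Two periods only | 3.0-4.9% | 3.6-5.1% | 6-25% | 3-5% |

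False positives are not materially inflated in either layout. Power is low in both. The interaction term means something different in each.

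**5. The interval for the mean difference.** Under similar assumptions (mean 1 to 4, rate halved), the 95% interval for the mean difference covered the truth in about 90-94% of trials. In 79-97% of trials it reached below minus the observed control mean, that is, to more falls prevented than the control arm had. Against the true control mean the share is 61-73%. These figures come from a plain two-arm comparison of the two-period mean, with no week-0 level. They describe a mean difference of skewed counts at 12 per arm and do not measure the baseline defect.

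**6. Would a standard count model do better?** On the same assumptions, negative binomial regression with Wald limits covered about 91-93%. Its type I error was roughly 7-9%, against 3-5% for the mean difference. Changing the model without a small-sample method would exchange one weakness for another.

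**The case against.** The best defence is that the layout can be rescued. Weekly calendars give two post-entry periods, and between-group differences at weeks 4 and 8 need no week-0 cell. A mean difference in falls is a legitimate quantity, and the ANOVA does not inflate false positives. All of this stands and limits the severity. It does not rescue the text: two periods are not all time points, and the sentence would still have to be changed for falls.

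A reader might infer stronger claims that the documents do not support:

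- *That the ANOVA is prescribed for the proportion of fallers.* The proportion is not among the eight variables and could be drawn in only through the words about all outcomes. That no method is named for it is an omission that a condensed article may leave to the full plan.
- *That incomplete diaries will be dropped or counted as full follow-up.* The article gives no rule on this. Follow-up is a fixed 8 weeks, and unequal diary time is an assumption.
- *That the 79-97% figure shows the size of the error.* As shown in step 5, it arises without any week-0 level and largely reflects the small sample.
- *That the trial's main conclusion is at risk.* Falls are the last-listed secondary outcome, and neither the primary analysis nor the sample size depends on them.

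**Conclusion.** The point holds in this form: the ANOVA stated for number of falls cannot be run as written, because the outcome has no week-0 value. This follows from setting Statistical analyses beside Secondary outcomes and needs no assumed fall rate. That a normal-theory mean difference is a poor summary here is a second, weaker point. It rests on falls being skewed with many zeros, and every simulated figure for it depends on assumed rates and dispersion.

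The consequence is an undefined level, a spurious time effect if zeros are entered, and an effect measure that is hard to interpret. It is not an excess of false positives. Severity: should be fixed before analysis, but it does not threaten the primary result.

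**What to change.** In Statistical analyses:

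1. Exempt number of falls from the repeated-measures ANOVA and state that it has no baseline value.
2. Compare total diary falls over weeks 1-8 between groups by a rate ratio, with diary time returned as exposure. Show weeks 1-4 and 5-8 as supporting splits.
3. Obtain both the p-value and the confidence interval by permutation or another small-sample method, not from negative binomial Wald limits.
4. Compare the proportion of fallers by a risk difference with an exact interval.
5. Present both as low-precision secondary results. With 12 per arm no method will be precise.

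Cost: wording only. The weekly calendars already supply the counts and the exposure, and no visit, participant or sample-size figure changes. The downsides are that falls are reported on a ratio scale, unlike the other outcomes, and that the interval takes slightly more work to compute.
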